**Figure 2 F2:**
[figure not shown]
Experimental set-up.

#### Anodal tDCS group

2.6.1

In the anodal tDCS group, anodal stimulation of the contralesional premotor cortex will be performed simultaneously with robotic-assisted therapy for 25 minutes. A constant current of 2 mA will be delivered for 25 minutes using the Ybrain tDCS System (Ybrain, Korea) via 2 saline-soaked electrodes. The anode will be positioned over the contralesional premotor cortex, which is 2.5 cm anterior to the C3 or C4 according to the international 10–20 EEG system. The cathode will be located in the ipsilesional supraorbital area.^[21]^

#### Sham tDCS group

2.6.2

Sham tDCS will be applied with the same configurations as anodal tDCS, except for the emission of a current for only 30 seconds.

### Assessment

2.7

Assessments will be conducted 3 times: at baseline (T0), after 2 weeks of intervention (T1), and at 4 weeks post-intervention (6 weeks post-baseline) (T2). The T0 assessment is conducted within 7 days before the start of the therapy session, the T1 assessment within 3 days after the end of the therapy session, and the T2 assessment within 7 days from day 30 after the start of the therapy session. At the T0 assessment, additional information on the participants’ baseline characteristics, including sex, age, stroke type, side of brain lesion, lesion area, stroke duration, and the initial National Institutes of Health Stroke Scale (NIHSS) score, will be collected. The NIHSS score measures neurologic deficits according to 11 categories, and the score ranges from 0 to 42, with 0 indicating no abnormality. Excellent specificity, sensitivity, and accuracy in predicting outcomes have been reported.^[22,23]^ As for the outcome measures, the primary outcome measure FMA-UE and all secondary outcome measures except the EEG laterality index (LI) (modified Rankin Scale [mRS], Korean version of the Modified Barthel Index [K-MBI], Brunnstrom stage of the arm and hand, the Box and Block Test [BBT], the Modified Ashworth Scale [MAS] of the wrist flexor/extensor, elbow flexor/extensor, and finger flexor, and the Medical Research Council [MRC] Scale of shoulder abduction, elbow flexion/extension, wrist flexion/extension, and finger flexion/extension) will be assessed 3 times. The EEG LI will be assessed twice, at T0 and at T1. Assessments last approximately 1.5 hours and regular breaks will be scheduled to mitigate fatigue and burden.

### Outcome measures

2.8

#### Primary outcome

2.8.1

The primary outcome is the change in FMA-UE scores between T0 and T1. The FMA-UE is a quantitative measure of motor impairment of the upper extremities, ranging from 0 to 66, with higher scores indicating less motor impairment.^[24]^

#### Secondary outcomes

2.8.2

Secondary outcomes are the change in FMA-UE scores between T0 and T2, and the changes in mRS scores, K-MBI scores, Brunnstrom stages, BBT scores, MAS scores of the wrist flexor/extensor, elbow flexor/extensor, and finger flexor, MRC Scale scores of shoulder abduction, elbow flexion/extension, wrist flexion/extension, and finger flexion/extension between T0 and T1 and between T0 and T2, as well as the change in the EEG LI between T0 and T1.

The mRS is a categorical measure of disability incorporating mental and physical status after neurological deficits. The scale consists of 6 grades, from 0 (no symptom at all) to 5 (severe disability), and 6 (death).^[25]^ The K-MBI is the Korean version of the MBI, which measures the degree of independence of ADL according to 10 items, with the total score ranging from 0 (completely dependent) to 100 (independent).^[26]^ The Brunnstrom stage is the motor recovery stages after stroke, with the recovery process classified into six stages from 1 (flaccidity with no movements of the limbs) to 6 (individual joint movements).^[27]^ The BBT is a measure of gross manual dexterity, assessed by counting the number of blocks moved from one compartment to another across the partition in 60 seconds, with proven validity.^[28]^ The MRC is an ordinal scale of muscle power, with proven reliability, and the MAS is a scale of spasticity which is graded from 0 to 4, larger numbers indicating more increased resistance to passive movement of the joints.^[29,30]^

The EEG LI will be calculated to measure the lateralization of cortical activity during rest and task performance. LI is calculated as LI = (NL-NR)/(NL+NR), and values range between −1 and 1. An LI > 0.2 indicates a predominance of right cerebral cortical activity, an LI < −0.2 indicates predominance of left cerebral cortical activity, and an LI between −0.2 and 0.2 is considered “not lateralized.”^[31]^

Participants will wear a cap with 32 channels of sensors and detectors placed according to the 10–20 system, and signals will be recorded using the LiveAmp system actiCAP Xpress Twist (Brain Products GmbH). The total EEG task design is as follows: Rest—Task with affected hand—Rest—Task with unaffected hand. For the resting state EEG acquisition, participants will remain seated comfortably on a chair. Each resting block consists of 1 minute with eyes closed and 1 minute with eyes open, and a total of 2 blocks are recorded for 4 minutes. Hand grasping is used as the target movement for the task, and the target movement posture will be shown on an LCD monitor to guide participants. Each task block consists of 10 hand grasping trials, with grasping durations of 3 seconds and intertrial intervals of 5 seconds. The inter-block interval is 1 minute, and a total of 4 blocks will be performed.

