### Statistical analysis

2.12

The primary analysis will be done on a modified intention-to-treat (ITT) population of participants who were randomly assigned to groups and underwent >1 therapy session. Participants who complete the 10 tDCS sessions and all 3 (T0, T1, and T2) assessments per protocol will be included for the secondary endpoint analysis to verify a sustained clinical response. For between-group comparisons of baseline characteristics, Student *t* tests or Mann–Whitney *U* tests for continuous variables and *χ*^2^ tests or Fisher exact test for categorical variables, depending on normality, will be used. Student *t* tests or Mann–Whitney *U* tests will be performed to investigate if the changes in primary and secondary outcome measures are different between the anodal tDCS and sham group. All statistical analyses will be performed using SPSS (version 25.0), and *P* values <.05 will be considered statistically significant. In the repeated measures analysis including assessments of T2, Bonferroni correction will be applied and the significance level will thus be adjusted to 0.05/2 = 0.025.

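### The EEG laterality index is referenced to anatomical left and right, so comparing its change between arms dilutes a contralesional effect; its printed reading also needs matching to its sign

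*Protocol article*

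**What the plan says.** All references are to the protocol article.

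- **Purpose of the index (2.8.2).** "The EEG LI will be calculated to measure the lateralization of cortical activity during rest and task performance".
- **Definition (2.8.2).** LI = (NL − NR)/(NL + NR), ranging from −1 to 1. NL and NR are not defined further.
- **Reading (2.8.2).** "An LI > 0.2 indicates a predominance of right cerebral cortical activity", while a value below −0.2 "indicates predominance of left cerebral cortical activity". Values in between count as not lateralized.
- **Endpoint (2.8.2).** One of the secondary outcomes is "the change in the EEG LI between T0 and T1".
- **Stimulated side (2.6.1).** The anode goes over the "contralesional premotor cortex, which is 2.5 cm anterior to the C3 or C4", so the stimulated side depends on the patient's lesion.
- **Eligibility (2.4).** The impairment must be unilateral; neither side is excluded.
- **Lesion side (2.7).** It is recorded at T0 as a baseline characteristic. No section uses it to re-sign or stratify the index.
- **Comparison (2.12).** The method is a two-sample t test or its rank-based counterpart (Mann–Whitney); these "will be performed to investigate if the changes in primary and secondary outcome measures are different between the anodal tDCS and sham group".

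**The concern.** The aim, the hypothesis and the electrode placement are all expressed relative to the lesion, and the EEG tasks are organised by affected and unaffected hand. The laterality index alone is expressed as anatomical left against right. The same biological response, a shift of activity towards the contralesional hemisphere, therefore raises the index in patients with one lesion side and lowers it in patients with the other. Averaging or ranking the change across a mixed arm sets these responses against each other.

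At stake is the interpretation of the only EEG outcome the article lists. A real contralesional effect could be reported as absent. A change that both arms share, such as spontaneous recovery, could show up as an arm difference if lesion side happens to be unbalanced.

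A second, separate matter is the direction label. On the plain meaning of N as hemispheric activity, the stated reading is opposite to the formula.

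**Working it through.** **Sample size behind the illustration.** Section 2.10 gives a difference of 9 to 10, SD 10, 80% power, two-sided 5% and 10% drop-out. At a difference of 10, n per arm = 2 × (1.960 + 0.842)² × (10/10)² = 15.7, so 16. Then 16/0.9 = 17.8, so 18 per arm and 36 in total, which reproduces the plan. These figures are for FMA-UE; they are used here only to fix 16 completers and 18 enrolled per arm. The article gives no effect size or SD for the laterality index.

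**Sign of the index.** Take N as activity.
- NL = 70, NR = 30: LI = 40/100 = +0.40. The left is larger, but the text reads this as right predominance.
- NL = 30, NR = 70: LI = −40/100 = −0.40. The right is larger, but the text reads this as left predominance.

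Both labels are reversed together. Swapping them changes no test statistic and no P value.

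**Dilution.** Let s = +1 for a right lesion (contralesional = left) and s = −1 for a left lesion. A contralesional shift d appears in the left/right index as s·d. If a share p of the active arm has s = +1, the mean is p·d − (1 − p)·d = (2p − 1)d. For the Mann–Whitney comparison, the excess of P(active > sham) over one half shrinks by the same factor (2p − 1), provided errors are identically distributed in the two arms and there is no shared change.

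**Illustrative power.** Assumptions: d = 1 SD, no shared change, the same p in both arms, two-sample t test, two-sided 5%. Because s varies between patients, the active-arm variance grows from 1 to 1 + 4p(1 − p)d². For example, at p = 0.6 it is 1 + 0.96 = 1.96; averaged with the sham variance of 1 this is 1.48, a pooled SD of 1.217. Power follows from the noncentral t distribution.

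| p | Expected difference | Pooled SD | Power, 16 per arm | Power, 18 per arm |
|---|---|---|---|---|
| Lesion-referenced (any p) | d | 1.000 | 0.78 | 0.83 |
| 0.5 | 0 | 1.225 | 0.05 | 0.05 |
| 0.6 | 0.2d | 1.217 | 0.07 | 0.08 |
| 0.7 | 0.4d | 1.192 | 0.15 | 0.17 |
| 0.8 | 0.6d | 1.149 | 0.30 | 0.33 |

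With d = 0.8 SD and 18 per arm, the lesion-referenced power is 0.65, against 0.05, 0.07, 0.13 and 0.25 at p = 0.5, 0.6, 0.7 and 0.8.

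**Plausible lesion mix.** If each side were equally likely (an assumption), an arm of 18 would have 6 to 12 left lesions with probability 0.90. At the edge of that range the retained fraction is 2 × 12/18 − 1 = 1/3, so in about 90% of such arms at most one third of d remains.

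**Shared change.** Suppose both arms also shift by g towards the contralesional side. The arm difference from g alone is [(2pA − 1) − (2pS − 1)]g = 2(pA − pS)g, where pA and pS are the shares with s = +1 in the active and sham arms.
- 10 v 8 of 18: 0.22g
- 11 v 7 of 18: 0.44g
- 12 v 6 of 18: 0.67g

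Randomization makes this zero on average, so it is chance error and not a systematic bias. Section 2.9 mentions no stratification by lesion side that would limit it.

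**The case against.** **N is undefined.** If N were a quantity that falls as activity rises, such as power in some frequency band, the printed reading would be right. Which EEG quantity is used is a detail an article may leave to a fuller document. This stands in part: a reader might infer that the formula and its reading are proven to contradict each other, and the text supports that only if N measures activity. It does not remove the need to state the direction, because the article says that the index measures activity and prints labels that clash on that meaning.

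**Re-signing may be planned elsewhere.** The trial is framed relative to the lesion throughout, so an analysis plan not shown might flip the index by lesion side. That is possible. But the article does not merely omit a detail; it prints an anatomical formula and an anatomical reading, which such a plan would have to override.

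**The effect need not cancel.** A reader might infer that the comparison wipes out the effect. That is so only at an exact 50:50 mix; otherwise it is diluted by |2p − 1|, and the article does not report the mix. The direction label plays no part in this dilution.

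**The power figures have no anchor.** The shift of 1 SD is assumed. The figures show the mechanism and do not measure this trial's loss. The (2p − 1) result does not depend on them.

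**The EEG aim is wider than this index.** The Introduction and Discussion speak of markers that separate responders from nonresponders, so it would be too strong to say that the whole secondary aim rests on this one comparison.

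**Conclusion.** The point holds as a should-fix on a secondary outcome. Followed as written, the plan compares an index whose sign depends on lesion side, and the expected arm difference for a contralesional shift d falls to (2p − 1)d: nothing at 50:50, 0.2d at 60:40, 0.4d at 70:30, and all of d only if every patient has the same lesion side. This rests on the printed left/right definition, on eligibility of either side, and on the absence of any stated re-signing; p itself is an assumption shown as a range. Chance imbalance in lesion side can add a spurious difference from any shift common to both arms.

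The direction label is a separate and lesser matter. If N is activity, the reading names the wrong hemisphere, which affects what would be concluded but not the test.

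A reader might take this as a threat to the trial's main conclusion. The documents do not support that: the primary outcome is the change in FMA-UE, the sample size is built on FMA-UE, and neither uses the laterality index.

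**What to change.** In section 2.8.2:

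1. Define the index as LI = (Ncontralesional − Nipsilesional)/(Ncontralesional + Nipsilesional), using the lesion side recorded at T0. Numerically this keeps the present index in right-lesion patients and multiplies it by −1 in left-lesion patients.
2. State what N is and whether it rises or falls with activity.
3. Correct the reading to match: if N measures activity, positive values mean contralesional predominance and negative values ipsilesional predominance.

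In section 2.12, state that the T0–T1 change in this lesion-referenced index is what is compared between arms.

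The cost is a few lines of wording and one line of analysis code. No new data are needed, because lesion side is already collected. The article reports recruitment as ongoing, so the change can be recorded before unblinding.

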### Randomization and blinding

2.9

The randomized allocation to the anodal tDCS group or sham tDCS group was generated using SPSS (version 25.0). Each group consists of 18 participants with a distribution ratio of 1:1, yielding a total of 36 enrolments. According to the randomized allocation, sealed opaque envelopes with a card representing the group assignment were prepared. When a participant is being enrolled, the principal investigator opens an envelope (in numerical order). Anodal tDCS and sham tDCS modules are marked as “A” and “B.” to mask the investigator who applies the tDCS to the participants, and the principal investigator tells the investigator whether “A” or “B” will be applied. Participants, occupational therapist who conduct the robotic therapy, and researchers who carry out assessments are also blinded to the group allocation.

### Sample size

2.10

The clinically important difference for the FMA regarding participants’ ability to move their arm has been reported as 9 to 10.^[32]^ A previous study on anodal tDCS or sham tDCS in patients with stroke revealed a standard deviation of 10.^[33]^ When estimating the drop-out rate as 10%, with a power of 80% at a 2-tailed significance level of 5%, the total required sample size is 36, that is 18 participants in each group.

### Safety and adverse events

2.11

A Data and Safety Monitoring Plan (DSMP) is established. Adverse events and data on the participants’ physical assessments will be monitored. Major non-compliance, adverse effects caused by a medical device, and unanticipated events will be reported within 15 days. Minor noncompliance and DSMP data will be reported every 6 months.

### Statistical analysis

2.12

The primary analysis will be done on a modified intention-to-treat (ITT) population of participants who were randomly assigned to groups and underwent >1 therapy session. Participants who complete the 10 tDCS sessions and all 3 (T0, T1, and T2) assessments per protocol will be included for the secondary endpoint analysis to verify a sustained clinical response. For between-group comparisons of baseline characteristics, Student *t* tests or Mann–Whitney *U* tests for continuous variables and *χ*^2^ tests or Fisher exact test for categorical variables, depending on normality, will be used. Student *t* tests or Mann–Whitney *U* tests will be performed to investigate if the changes in primary and secondary outcome measures are different between the anodal tDCS and sham group. All statistical analyses will be performed using SPSS (version 25.0), and *P* values <.05 will be considered statistically significant. In the repeated measures analysis including assessments of T2, Bonferroni correction will be applied and the significance level will thus be adjusted to 0.05/2 = 0.025.

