### Intervention

2.6

All participants will receive 25 minutes of robot-assisted therapy with the ArmeoPower device (Hocoma, Volketswil, Switzerland), daily on weekdays for 2 weeks, for a total of 10 sessions. The robot-assisted therapy will be managed by the same experienced occupational therapist who will choose the adequate program for each participant. According to the participant's group allocation, anodal tDCS or sham tDCS will be applied concurrently with the robot-assisted therapy. The experimental setup is demonstrated in Figure 2. The time used to adjust the tDCS setup and the robotic arm will not be counted as therapy time. All subjects will undergo an additional 30 minutes of conventional occupational therapy and will be permitted to engage in physical therapy to restore gait during the intervention period. Intervention will be halted at any time, on the participant's request or on the primary investigator's decision, upon any severe adverse events.

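### Section 2.12 pairs a session-defined modified ITT set with a T0–T1 change test that, as stated, can use only patients with a T1 score, and limits the T2 analysis to completers

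*Protocol article*

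**What the plan says.** All references are to the protocol article.

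- Section 2.8.1 (Primary outcome): "The primary outcome is the change in FMA-UE scores between T0 and T1".
- Section 2.12 (Statistical analysis), primary set: a "modified intention-to-treat (ITT) population of participants who were randomly assigned to groups and underwent >1 therapy session". A T1 score is not a condition of membership.
- Section 2.12, test: Student t or Mann–Whitney "tests will be performed to investigate if the changes in primary and secondary outcome measures are different between the anodal tDCS and sham group". No baseline adjustment is named.
- Section 2.12, sustained response: "Participants who complete the 10 tDCS sessions and all 3 (T0, T1, and T2) assessments per protocol will be included for the secondary endpoint analysis". The same section mentions a repeated measures analysis that includes T2, tested at 0.025, but the only outcome tests it names are the two-sample tests of change.
- Section 2.10 (Sample size): the important difference in FMA "has been reported as 9 to 10" points, the SD is 10, power is 80% at two-sided 5%, and 10% drop-out is allowed for, giving 18 per group.
- Section 2.6 (Intervention): "Intervention will be halted at any time, on the participant's request or on the primary investigator's decision, upon any severe adverse events".
- Section 2.7 (Assessment): "the T1 assessment within 3 days after the end of the therapy session". T2 follows later. The article does not say whether a patient who stops early is still assessed, or from which day that patient's T1 window would be counted.

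**The concern.** A two-sample test on change scores needs both scores. A patient with two sessions and no T1 score belongs to the named primary set but has no value to put into the named test. Unless a rule elsewhere supplies one, the test runs on those with T1 under a modified ITT label.

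Three things are at stake. First, stopping may depend on arm, tolerance or recovery, so those who reach T1 may not be a fair sample of those randomised. Second, a patient with T0 and T2 but no T1 contributes nothing to the primary comparison, and nothing to the T2 comparison either, since that requires all three assessments. Third, the T2 comparison is conditioned on completing treatment, so it no longer compares the groups as randomised.

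**Working it through.** **1. The plan's own figure.** Inputs from Section 2.10: SD 10, two-sided 5%, power 80%, difference 9 to 10, drop-out 10%.

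n per arm = 2 × (1.960 + 0.842)² × (SD / difference)².

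- Difference 10: 2 × 7.85 × 1 = 15.7, so 16. Then 16 / 0.9 = 17.8, so 18 per arm and 36 in total. This is the stated figure.
- Difference 9: 2 × 7.85 × 1.235 = 19.4, so 20. Then 20 / 0.9 = 22.2, so 23 per arm and 46 in total. This is not the stated figure.

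The stated 36 therefore corresponds to a difference of 10 with 16 analysable per arm. Inflating in this way treats those lost as adding nothing to the test. That fits an analysis of patients with T1 scores but does not prove that one is intended.

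**2. Power if 10% have no T1.** With 16 per arm and a difference of 10, power is 0.807 (normal approximation) or 0.781 (t test). With all 18 per arm it is 0.851 or 0.830. The loss is the one the sample size was built to absorb.

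**3. Possible bias.** Ten per cent of 18 is 1.8, about 2 per arm. Let the gap be how much less the missing patients would have changed than the completers of the same arm. The documents give no such figure; 5 to 10 points is an assumption. All loss is placed in one arm.

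Bias in that arm's mean = gap × missing / 18.

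| Missing in one arm | Gap 5 | Gap 10 |
|---|---|---|
| 1 | 5 × 1/18 = 0.28 | 10 × 1/18 = 0.56 |
| 2 | 5 × 2/18 = 0.56 | 10 × 2/18 = 1.11 |
| 3 | 5 × 3/18 = 0.83 | 10 × 3/18 = 1.67 |

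Three missing of 18 is 17% of that arm, above the planned rate.

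**4. Bias against precision.** With SD 10, the standard error of the difference is 10 × √(1/16 + 1/16) = 3.5 with 16 per arm, or 10 × √(1/16 + 1/18) = 3.4 with loss in one arm only. For 2 missing in one arm, the bias is 0.56 / 3.44 = 0.16 to 1.11 / 3.44 = 0.32 standard errors. At 0.32, a nominal two-sided 5% test rejects with probability P(Z > 1.96 − 0.32) + P(Z < −1.96 − 0.32), which is about 0.051 + 0.011 = 6.2%. Similar losses in both arms would partly cancel.

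**The case against.** A reader might infer that the plan discards everyone without T1, that it is a complete-case analysis by design, and that this contradicts the planned 10% drop-out. The documents do not support that reading.

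- No sentence says that patients without T1 are dropped, and none rules out imputation. A missing-data rule may sit in a full protocol or SAP that is not shown, and its absence from a condensed article is not a finding.
- The completer restriction is written only for the sustained-response analysis, not for the primary one.
- Section 2.6 halts the intervention. It does not halt assessment, so stopping stimulation need not mean a missing T1.
- The 10% is built into the sample size and is not tied to T1. It may include patients lost before a second session, who are outside the set, or lost after T1. T1 also comes after only two weeks of weekday sessions in patients recruited as inpatients, so fewer than 10% of the set may lack it.
- The size of the bias depends on assumed gaps and one-sided loss.
- A mixed model does not recover a patient with no score after baseline, and it assumes data missing at random, which is the very assumption in doubt.

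All of this stands, and it limits the point. It does not remove the mismatch: the article states a set and a test, and the test as stated cannot take every member of the set. Nor does it touch the explicit completer-only rule for T2. The limits of the model are met by a sensitivity analysis, not by keeping a test that uses less of the data.

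**Conclusion.** The point holds in limited form. As stated, the primary test can use only the members of the modified ITT set who have a T1 score, and the T2 analysis is confined to patients who completed treatment and all visits. Power at a difference of 10 is not compromised.

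The possible bias is about 0.6 to 1.1 points if 2 of 18 are missing in one arm only with a gap of 5 to 10 points. That is at most about a third of a standard error, and small beside a target of 9 to 10 points. The case for change rests less on that figure than on the availability, at little cost, of an analysis that follows randomisation more closely and uses the T0 and T2 scores already scheduled. It is worth changing while recruitment is ongoing, but it does not undermine the trial.

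**What to change.** Replace the change-score test and the completer-only T2 analysis of FMA-UE by one mixed model for FMA-UE at T1 and T2, with T0 FMA-UE, arm, visit and arm-by-visit. Fit it to all randomised patients with any post-baseline score. This also removes the exclusion of patients who had no more than one session. Take the T1 contrast as primary and the T2 contrast as secondary, and say which of the two significance levels in Section 2.12 applies to each. With T0 in the model, the arm contrast in the T1 score equals the arm contrast in the T0–T1 change, so the primary outcome is not altered.

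State in Section 2.7 that the scheduled T1 and T2 assessments are still done in patients whose stimulation was stopped, and from which day their T1 window is counted. This should be settled now, because a missed score cannot be recovered later.

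Add a sensitivity analysis that gives patients with no post-baseline score a range of assumed changes, for example 0 to 10 points, varied separately by arm. A single value of zero is not clearly conservative: these are subacute patients and both arms receive active rehabilitation, so some gain is plausible without stimulation.

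Cost: analysis wording, a standard model in the named software, and no visits beyond those scheduled. Downside: the model assumes missing at random and cannot recover patients with no post-baseline score, hence the sensitivity analysis.

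### The primary population requires more than one therapy session, so a randomised patient who stops after a single session is left out of the primary endpoint

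*Protocol article*

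**What the plan says.** Section 2.12 (Statistical analysis) names the set for the primary analysis: "The primary analysis will be done on a modified intention-to-treat (ITT) population", made up of "participants who were randomly assigned to groups and underwent >1 therapy session". The only other analysis set in that section, for the sustained-response endpoint, is narrower: "Participants who complete the 10 tDCS sessions and all 3 (T0, T1, and T2) assessments per protocol will be included". No analysis of all randomised participants is stated.

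Section 2.6 (Intervention) schedules robot therapy "daily on weekdays for 2 weeks, for a total of 10 sessions", with active or sham tDCS applied during each session. The arms differ only in current. In the active arm (2.6.1), "A constant current of 2 mA will be delivered for 25 minutes". Sham (2.6.2) uses the same configuration "except for the emission of a current for only 30 seconds". Section 2.6 also provides for stopping: "Intervention will be halted at any time, on the participant's request or on the primary investigator's decision, upon any severe adverse events".

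The primary outcome (2.8.1) is the change in FMA-UE from T0 to T1.

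**The concern.** The number of sessions a patient attends is known only after treatment has begun, so it is not a baseline fact. A threshold of more than one session removes two groups of randomised patients: those with no session and those with exactly one. The first group left before any stimulation, so under blinding its loss should not depend on arm. The second group left after one full exposure to its assigned stimulation, so its loss may be a consequence of that stimulation. A threshold of at least one session would keep the second group; the threshold as written drops it.

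At stake is the protection that randomisation gives the primary comparison. With 18 patients per arm, each exclusion is 1/18 = 5.6% of an arm. The completer set cannot bring these patients back, because it requires all 10 sessions.

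**Working it through.** **Inputs from the protocol article.** 18 per arm, 1:1 (2.9). Clinically important difference 9 to 10 points, SD 10, drop-out 10%, power 80%, two-sided 5% (2.10). **Assumed, because the document is silent:** the number k of one-session stoppers excluded from an arm, and the number g of points by which they would have done worse than the patients kept.

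**1. The plan's own figure.** n per arm = 2 × (1.960 + 0.842)² × 10² / 10² = 15.7, rounded up to 16. Allowing for 10% drop-out, 16 / 0.9 = 17.8, rounded up to 18 per arm, 36 in total. The stated 36 is reproduced at a difference of 10.

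**2. Power is hardly affected.** With 18 sham patients and 0, 1, 2 or 3 exclusions from the active arm, t-test power at a difference of 10 is 83.0%, 81.9%, 80.6% and 79.1%. The issue is possible bias.

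**3. Shift in one arm's mean.** Let the patients kept have mean m and the k excluded have mean m − g. The full-arm mean is [(18 − k) × m + k × (m − g)] / 18 = m − k × g / 18. The analysed mean therefore exceeds the full-arm mean by k × g / 18.

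| k | g = 5 | g = 10 |
|---|---|---|
| 1 | 0.28 | 0.56 |
| 2 | 0.56 | 1.11 |
| 3 | 0.83 | 1.67 |

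Relative to a planning difference of 10, the values 0.28 and 1.11 are about 3% and 11%. The standard error of the difference with 18 per arm is 10 × √(2/18) = 3.33, so 1.11 is about one third of a standard error.

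**4. Direction.** With exclusions in both arms, the bias in active minus sham is (k_active × g_active − k_sham × g_sham) / 18. It is zero if losses and prognosis match across arms. It favours active stimulation if the first term is larger and sham if the second is. Nothing in the document fixes which.

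**5. Error rate in the one-sided case.** Simulation (40,000 runs, no true difference, SD 10, t test, exclusions from the active arm only) gave these chances of a significant result favouring active stimulation, against about 2.5% with no exclusions:

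| k | g = 5 | g = 10 |
|---|---|---|
| 1 | 3.0% | 3.6% |
| 2 | 3.5% | 4.8% |
| 3 | 4.3% | 6.6% |

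**6. How often the rule would bite.** If the chance of stopping after the first session in an arm is r, the chance of at least one such loss among 18 is 1 − (1 − r)^18. This is 31% for r = 2%, 60% for r = 5% and 85% for r = 10%. These rates are also assumed.

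**The case against.** The strongest reply is that the rule may do little harm. The document gives no tolerability or early-stop rate for either arm. Sham uses the same set-up with a brief current, and section 2.9 describes participants, the therapist, the investigator applying tDCS and the assessors as blinded, all of which reduces differential stopping. The planned 10% drop-out is 0.1 × 18 = 1.8 patients per arm for all causes, so the case k = 2 in one arm spends roughly the whole allowance on the first session. Stopping after later sessions can depend on arm just as well. The threshold may also be a slip for at least one session, and the article calls the set modified and defines it on the spot, so the label misleads nobody.

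Most of this stands, and it limits what can be claimed. A reader might infer that first-session stopping is the loss most likely to depend on arm, or that the rule tends to favour active stimulation. The documents support neither. They give no arm-specific stopping figures, and under no treatment effect a bias arises only if stoppers also have a different prognosis, which is not stated. Nor does section 2.6 say that a halted patient loses the T1 assessment.

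The reply does not remove the rule itself. The text sets the primary population on an event that follows treatment. Blinding is also not complete on this point: the principal investigator opens the allocation envelope and is not listed among the blinded roles, and section 2.6 gives the primary investigator a part in halting treatment. If these are the same role, a halt after one session could be made with knowledge of the arm and would take the patient out of the primary analysis. If the threshold is a slip, the published wording still needs correcting before anyone has to choose between the two readings with data in hand.

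**Conclusion.** The point holds as a defect in the stated definition of the primary population. Taken literally, the rule excludes a randomised patient treated exactly once, after the arms had diverged, and no wider set is stated that would restore the full randomised comparison. That loss can depend on arm.

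Size and direction are unknown. The range of 0.28 points (one exclusion, 5 points worse) to 1.11 points (two exclusions, 10 points worse) assumes that all exclusions fall in one arm. Matching losses in both arms would cancel, and no such losses would mean no bias. Power is not a reason for concern. The change is worth making because it is cheap and recruitment was still under way at submission (2.2), not because a large bias has been shown.

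**What to change.** In section 2.12, define the primary population as all randomised participants, analysed in their assigned arm. At minimum, replace >1 with ≥1 therapy session. State that the planned T1 assessment will be sought from participants who stop treatment. Keep the >1-session set, if wanted, as a sensitivity analysis only.

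The definition itself is a change of one phrase and leaves the sample size at 36. The further costs are T1 follow-up of the few who stop and a slight dilution of the estimated effect by patients who received little treatment. How to handle those with no T1 value can be left to the analysis plan.
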